# Community-engaged optimization of COVID-19 rapid evaluation and testing experiences: roll-out implementation optimization trial

**DOI:** 10.1186/s13012-023-01306-y

**Published:** 2023-10-02

**Keywords:** Implementation science, COVID-19, Underserved communities, Health equity, Promotores, Testing, Roll out implementation optimization design, RE-AIM framework

## Abstract

**Background:**

There continues to be a need for COVID-19 testing that is pragmatic, community-centered, and sustainable. This study will refine and test implementation strategies prioritized by community partners: (1) walk-up no-cost testing, (2) community health worker (promotores)-facilitated testing and preventive care counseling, (3) vending machines that dispense no-cost, self-testing kits.

**Methods:**

A co-designed Theory of Change from an earlier study phase and the Practical, Robust Implementation and Sustainment Model (PRISM) will guide the study design, measures selection, and evaluation. The first aim is to refine and operationalize a multi-component implementation strategy bundle and outcome measures for COVID-19 testing. A Community and Scientific Advisory Board (CSAB) will be established and include community members, clinical providers/staff from the partnering Federally Qualified Health Center (FQHC), public health researchers, policymakers, and a county health department ambassador. Engagement of CSAB members will be assessed through structured ethnography and a survey about the quality and quantity of engagement practices. The second aim is to implement and evaluate the impact of the implementation strategy bundle to optimize COVID-19 testing in communities using a roll-out implementation optimization (ROIO) design. Seven thousand and five hundred community members will be enrolled across four FQHC clinics over 18 months. Participants will be invited to complete an electronic survey about their demographics, health, and COVID-19 testing results and experiences. CSAB members and clinic partners will participate in PRISM fit and determinant assessments prior to each clinic rollout and post-trial. Interviews will be conducted with 60 community participants and 12 providers/staff following a 3-month rollout period at each clinic, inquiring about their experiences with the implementation strategies. Quantitative data will be analyzed using hierarchical multilevel models to determine the impact of implementation strategies. Qualitative data will be analyzed using rapid qualitative approaches to summarize implementation experiences and identify necessary changes prior to subsequent rollouts. A matrix approach will be used to triangulate data from quantitative and qualitative sources based on PRISM domains.

**Discussion:**

This is one of the first pragmatic implementation trials to use a ROIO design and aims to co-create a sustainable and equitable COVID-19 testing program. Findings are likely to generalize to other public health prevention efforts.

**Trial registration:**

NCT05894655 March 2, 2023.

Contributions to the literature
• This study integrates unique and complementary methods from community engagement, implementation science, epidemiology, clinical research, and data science to refine, implement, and sustain a multilevel, multicomponent implementation strategy bundle to optimize COVID-19 testing among underserved communities.• This study uses a novel roll-out implementation optimization design that balances rigor and responsiveness to the needs of the community and the changing pandemic context to reduce COVID-19 testing disparities.• This study’s findings have strong potential to generalize to other public health prevention efforts to mitigate health disparities for underserved communities.

## Background

### COVID-19 disparities experienced by underserved communities in California

COVID-19 health inequities abound in low-income, ethnic minority communities. The residents of San Diego who have been most impacted by COVID-19 also experience high rates of poverty, limited educational attainment, are employed in essential and service jobs that require frequent in-person contact, and frequently live in multi-generation households, all of which have exacerbated COVID-19 health disparities with regards to transmission, infection, and negative health sequelae [1]. Throughout the COVID-19 pandemic, rates of COVID-19 have been persistently high in San Diego County’s central and southern communities near the USA/Mexico border.

### Value of community engagement methods to reduce health disparities

Meaningful community engagement is essential to the implementation and sustained use of interventions designed to address health inequities [2, 3]. Community engagement is not a trivial undertaking, especially with underserved communities whose perspectives have historically been excluded from public health planning. Authentic and impactful community engagement requires investment of specialized resources, personnel, and time [4], particularly into activities such as nurturing partnerships with community engagement practitioners to foster relationships between community members and researchers, compensation for community member participation in planning, design and evaluation activities, and interpretation and translation services to encourage equitable participation from individuals in their preferred languages. Community engagement methods vary in their form, intensity, and duration, but typically have a shared goal of “involving communities in decision-making and in the planning, design, governance, and delivery of services; community engagement activities can take many forms, including service user networks, health-care forums, volunteering, or interventions delivered by trained peers” [5].

### Need for development and implementation of strategies for optimal use of COVID-19 testing (evidence-based practice)

The prolonged course of the COVID-19 pandemic, which has been punctuated by several viral variant-driven surges, has illustrated the need for sustainable, long-term, and flexible COVID-19 testing infrastructure and services. Key features of public health testing infrastructure comprise accuracy (including high sensitivity for asymptomatic/pre-symptomatic individuals); temporal and geographic accessibility; low cost; rapid return of results that are easy to understand; and reportability to enable public health agencies to track and respond to changes in the pandemic.

Polymerase chain reaction (PCR) and rapid antigen tests (RATs) are the major COVID-19 testing methods, and they differ markedly in testing features. PCR tests are highly accurate with results reported to clinical providers and public health authorities, with a moderately rapid turnaround time (< 24 h for this study team’s testing lab). However, they are relatively expensive, typically performed at specific and limited locations during certain time windows (often requiring an appointment), and often require insurance coverage and a healthcare provider visit. In contrast, RATs are fast (providing results in 15 min), inexpensive, and can be self-administered using a portable and storable kit. However, they are less sensitive, and results are typically not reported to clinical providers or public health authorities, likely resulting in undercounting of cases. An ideal COVID-19 testing program will take advantage of these complementary testing methods and employ strategies to promote optimal test selection and use.

### Community-driven optimization of COVID-19 testing to reach and engage underserved areas for testing equity (CO-CREATE, phase 1 study)

The current study extends from the CO-CREATE phase 1 study. CO-CREATE was a 2-year study funded through the National Institutes of Health Rapid Acceleration of Diagnostics for Underserved Populations (RADx-UP) initiative. The objective was to understand practices and determinants to uptake of walk-up no-cost COVID-19 testing for underserved communities in partnership with a federally qualified health center (FQHC) near the US/Mexico border. In the phase 1 study, a 22-member Community and Scientific Advisory Board (CSAB) was established and met monthly to participate in an Appreciative Inquiry method led by the Global Action Research Center (ARC), a community partner and social change organization. The findings from this co-creation process were implemented at a walk-up no-cost COVID-19 testing site, which resulted in the administration of 24,422 tests performed (> 13,253 unique participants) over a 2-year timeframe. Details about the phase 1 study and CSAB are reported elsewhere [6–8].

### Implementation strategies

The current study will refine and test three implementation strategies for optimal COVID-19 testing (evidence-based practice): (1) walk-up no-cost testing, (2) Community Health Worker (Promotores)-facilitated testing and preventive care counseling, (3) vending machines that dispense no-cost, self-testing kits. These strategies were prioritized by the CSAB of the phase 1 study using implementation mapping [9].

#### Walk-up no-cost testing protocol

A no-appointment, walk-up point-of-care rapid testing at the partnering FQHC will continue at clinic 1 based on the success of the phase 1 study. Testing will be offered several times per week and titrated to lower intensity following the first clinic rollout. Trained, bilingual staff will oversee the on-site testing protocol. The walk-up testing protocol will not be offered at the other clinic sites.

#### Promotora-facilitated testing and preventive care counseling

Trained, bilingual promotores will provide health counseling on these topics: when COVID-19 testing is recommended; which test to use; testing instructions; and how to interpret the results. Promotores will also offer general preventive care reminders, such as flu shots, blood pressure checks, and hemoglobin A1c screenings. Promotores will be available full-time during clinic working hours throughout the first 3 months of roll-out at each clinic and subsequently available on an as-needed basis.

#### Vending machines that dispense no-cost self-testing kits

Vending machines located outside of clinics will provide interactive instructions in Spanish and English for accessing no-cost self-administered COVID-19 test kits. The vending machines will be available 7 days/week and will be accessible to the public. The vending machine locations will be identified with guidance from the partner FQHC to consider potential workflow and service implications. Study registration and consent will be required to obtain a test kit from the vending machines. Alternative sources for testing kits will be provided for individuals who do not want to register and consent to the study.

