### Setting

This study will be conducted in partnership with a high-performing FQHC that serves low-income and uninsured San Diegans and has a long-standing relationship with the lead university. For this study, we will focus on clinics in Central and South San Diego. As shown in Table 1, the 4 target clinics serve primarily Latino and Black patients, and a large proportion report Spanish as their primary language. Preventive healthcare rates for commonly recommended adult preventive screenings and immunizations are low, particularly for blood pressure (*M* = 60.6% across clinics) and flu immunization (*M* = 20.4% across clinics) [18].

**Table 1 Tab1:** FQHC clinic characteristics

	Clinic 1	Clinic 2	Clinic 3	Clinic 4
Total # patients	18,124	20,102	8328	8120
Patient race/ethnicity				
Latino	91.6%	79.0%	61.2%	74.3%
Black	1.3%	3.0%	16.9%	12.1%
Asian	1.5%	4.7%	4.7%	2.2%
White	14.4%	15.0%	29.4%	15.3%
Patient preferred language				
Spanish	70.1%	56.7%	36.0%	48.8%
Adult preventive health services (% of “active” patients who completed a medical visit and had a preventive health service in the past 18 months)				
Blood pressure screening	55.4%	62.3%	58.2%	66.3%
HbA1c screening	78.9%	79.3%	72.8%	81.6%
Flu immunization	25.0%	15.5%	16.2%	24.9%
COVID-19 cases/100,000 (2/20–4/22)	48,219	31,623	34,209	35,716
RATs distributed since 1/22	785 (*M* = 196/month)	499 (*M* = 125/month)	244 (*M* = 61/month)	192 (*M* = 48/month)

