#### Data collection

Quantitative and qualitative data will be collected using multiple databases and methods. Data collection methods are summarized in Table 2 with the data source name, type of data collected, origin of data and timing for data collection, and associated PRISM domains assessed. Data from the PRISM Fit Assessment will be summarized as descriptive statistics and displayed in the form of bar graphs to inform the group action planning discussion. Key implementation and clinical and public health effectiveness outcomes are summarized in Table 3. The timing for each data collection method is also noted in Fig. 1. Participants will be required to provide contact information and minimum symptom and exposure data prior to obtaining rapid tests and the type of test and timing of testing will be captured for both the walk-up onsite testing and vending machine testing along with basic demographics. Participants will also be invited to provide rapid test results and receive personalized health counseling based on their test result.

**Table 2 Tab2:** Data sources, data types, origin and PRISM domains

Data source name	Type	Origin/timing	PRISM domains
REDCap study database for rapid COVID-19 testing (QUAL + QUANT)	Database completed by walk-up onsite testing staff about number of tests completed, reason and timing for testing including symptoms and exposure, community member demographics	Walk-up onsite testing staff Ongoing	Reach Implementation Maintenance
Preventive care status and health characteristics (QUANT)	Electronic health records data on primary and secondary outcomes, participant demographics, other health characteristics	SYH Research Assistant accessing electronic health records After each initial roll-out	Reach Recipient characteristics Effectiveness
Promotore support activities database (QUAL + QUANT)	# of days and hours promotore services are provided; # and type of support activities	Promotores Ongoing	Adoption Implementation Maintenance
Vending machine automatic data log (QUANT)	#, timing, type of interactions with vending machine; reason and timing for testing, type of test used; participant demographics	Programmed in vending machine Ongoing	Reach Effectiveness Implementation Maintenance

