	Maintenance	Ongoing operation of walk-up onsite testing beyond initial roll-out at Clinic 1; ongoing promotore services provided beyond initial roll-out (first 3 months) at all clinics (and type of support); ongoing operation of vending machines beyond initial roll-out (first 3 months)
Effectiveness (clinical and public health) outcomes	COVID-19 RAT completion	Number of RATs distributed through the walk-up onsite testing and vending machines
	Optimal COVID-19 testing experience	Offering the most clinically useful COVID-19 test and returning results within an optimal timeframe to enable appropriate treatment and decrease transmission, in the most acceptable, timely, and feasible manner
	Preventive care engagement	Up-to-date age/sex-specific preventive care (e.g., flu shot; cancer screening) based on participants’ demographic and health characteristics

Qualitative interviews with patients/community members and clinic providers/staff will be conducted after each initial roll-out period (after 3 months of implementation) to understand their experiences with the implementation strategy bundle and identify potential areas for improvement. A total of 60 interviews with patients/community members evenly recruited from each of the 4 clinics will be conducted. Patients/community members will be identified for interviews based on their interest expressed when initially obtaining tests as part of the walk-in onsite clinic or vending machine. An additional set of interviews will be conducted with 12 providers/staff (3/clinic) identified based on their involvement in supporting the implementation or having exposure to the implementation strategy bundle.

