#### Data analysis

Quantitative data from study databases will be summarized using simple descriptive statistics including frequencies, measures of central tendency, and variability along with data visualization methods, such as frequency tables, bar charts, line graphs, and scatter plots to understand patterns and characteristics of testing uptake, exposures, and symptoms and to guide adaptive implementation. Missingness in data will be examined via sensitivity analysis and imputation methods will be applied when appropriate. Parametric and non-parametric tests will be employed to compare the survey responses between the clinics while controlling for a variety of demographic and socioeconomic variables, including the FQHC clinic cluster. Data collected at the point of test distribution (collected by study coordinators, promotores, and vending machines) will be used to evaluate implementation strategy effectiveness on testing uptake. Hierarchical multilevel models will be used to ensure the inclusion of random effects, variation between clusters, variation between times within clusters, and the fixed effect of time which will be estimated independently of treatment effect so that systematic change over time will not be mistaken for effect of treatment. This is key, based on significant variations in testing uptake observed during previous COVID-19 variant waves. To account for potential within-clinic correlation, data will be reduced for each cluster to a single observation, and then subject to standard two-sample analyses. Secondary analyses will be conducted to determine the appropriateness of the test type distribution within the context of symptom onset and exposure time frame.

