### Power size calculations

The number of participating clusters/clinics and target clinic participant enrollment for the ROIO study design was determined using cluster randomized trial sample size estimation tools. Per the ROIO study design, each clinic cluster will begin in the control group and then cross over into the intervention group at different time points and then continue with the intervention until the end of the study (see Fig. 2). Although it is anticipated that the implementation strategies as outlined by CSAB will undergo some adjustments during the implementation process, the target cluster/clinic sample size estimates are based on a stepped wedge design using serial cross-sectional evaluations of electronic medical records and test kits distributed. It is estimated that the study will have the capacity to distribute 52,000 FDA-authorized rapid antigen tests provided by the San Diego County Health and Human Services and the California Department of Public Health. The primary outcome is the increased distribution of RATs within the communities near each of the 4 clinics. This will be measured using a proxy outcome defined as the proportion of clinic patients visits to the number of RAT kits distributed per month at each participating clinic. Currently, RAT kit distribution among target clinic patients ranges from 7 to 13% (*M* = 9%) with approximately 430 kits being distributed per month between all four clinics. The aim is to increase distribution of test kits to 40% of clinic patient encounters per month, which would result in the distribution of 1822 kits per month during the final treatment sequence. Based on data collected from the phase 1 study, approximately 40% of testing uptake occurred among clinic patients and the remaining 60% from community members even when the intervention was clinic-based. It is anticipated that there will be a similar community uptake during this study. Based on the sequential rollout outlined in the Fig. 2 with rollout for Clinic 1 at month 4, Clinic 2 at month 8, Clinic 3 at month 12, and Clinic 4 at month 16, over the course of the entire study it is anticipated that a total distribution of 20,503 tests, assuming average distribution per clinic. Estimating that this will equal approximately 40% of total increase and the remaining uptake to occur among community members, a total uptake of 58,091 test kits is estimated over the course of the study. Using the Shiny CRT Calculator [24], it was determined that a minimum cluster sample size of 285 across 4 clinics will provide sufficient power (beta > 0.8) to determine an intervention proportion increase of 0.05 to 0.25 assuming the following: stepped-wedge design, cross-sectional sampling structure at each of 4 sequences (approximately every 3 months in the study), 0.5 coefficient of variation in cluster sizes (based on average number of patient encounters per month per clinic), intra-cluster correlation (ICC) of 0.02, for our binary outcome (test or no-test). It was also assumed that there will be an exchangeable cluster correlation structure as SARS-CoV-2 testing demand has been impacted significantly by changes in variant severity and transmissibility.

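### The RAT-distribution numerator is defined two ways, and kits given to people who decline study consent fall outside one of them, so control and intervention periods may not be counted alike

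*Protocol article*

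**What the plan says.** All references are to the protocol article.

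- **Objective.** Power size calculations: "The primary outcome is the increased distribution of RATs within the communities near each of the 4 clinics". The proxy there relates RAT kits distributed per month at each clinic to clinic patient visits. It names no channel and sets no consent condition.
- **Baseline.** The same section gives about 430 kits a month over the four clinics, a mean of 9%. The counts behind it are in Table 1 (Setting), in the row "RATs distributed since 1/22".
- **Outcome table.** Table 3 (Data collection) defines RAT completion as "Number of RATs distributed through the walk-up onsite testing and vending machines".
- **Condition on vending kits.** The vending machine section says: "Study registration and consent will be required to obtain a test kit from the vending machines". It continues: "Alternative sources for testing kits will be provided for individuals who do not want to register and consent to the study". The sources are not named.
- **Data required before a test.** Data collection: "Participants will be required to provide contact information and minimum symptom and exposure data prior to obtaining rapid tests".
- **Analysis source.** Data analysis: "Data collected at the point of test distribution (collected by study coordinators, promotores, and vending machines) will be used to evaluate implementation strategy effectiveness".
- **Channels by clinic.** The walk-up section confines walk-up testing to Clinic 1. Of Table 3's two channels, Clinics 2 to 4 therefore have only the vending machine.

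**The concern.** A stepped-wedge contrast needs the outcome counted in the same way before and after crossover. Here the two definitions differ.

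The power section counts every kit handed out at the clinic. Table 3 counts kits from two named channels, and one of those releases a kit only to a person who has joined the study. Someone who comes to the machine, declines, and is given a kit elsewhere has received a kit in the community, which is what the stated objective is about. Table 3 does not count that kit.

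The baseline kits cannot have been subject to consent to this study. If the intervention period is counted by Table 3 and set against that baseline, the loss falls in the intervention period only and does not cancel. It may also differ by clinic, because Clinic 1 has a second counted channel and the others do not. What is at stake is the meaning of the estimate more than its precision: it could describe kits taken by people willing to enrol, compared with all kits.

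**Working it through.** **1. Baseline reproduced.** Table 1 gives 785, 499, 244 and 192 kits, with monthly means of 196, 125, 61 and 48. Since 785/196 ≈ 4, the counts cover four months. (785 + 499 + 244 + 192)/4 = 1720/4 = 430 a month, as stated. Four months from 1/22 ends well before the registration date of March 2, 2023, so these kits were not conditional on consent to this trial. The article does not say how they were handed out.

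**2. Target reproduced.** 1822 kits at 40% of encounters implies 1822/0.40 = 4555 encounters a month. Then 430/4555 = 9.4%, in line with the stated 9%. The planned effect is 40 − 9 = 31 points.

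**3. The two numerators side by side.**

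| Kit | Power section (all kits at the clinic) | Table 3 (walk-up and vending) |
|---|---|---|
| Baseline kit at Clinics 2–4 | counted | no walk-up there, and vending belongs to the bundle |
| Vending kit, consented | counted | counted |
| Decliner's kit, issued at the clinic | counted | not counted |
| Decliner's kit, issued off-site | not counted | not counted |

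The definitions disagree in the first and third rows.

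**4. Would any listed source record a decliner's kit?** In Table 2, the REDCap database covers walk-up testing and the machine log covers machine interactions. The promotores' database covers days, hours and support activities. None is described as recording kits from alternative sources.

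**5. Size if kits go uncounted.** Let r be the share of intervention kits that go uncounted. The documents give no value, so the range below is an assumption. It also treats 40% as the true rate with every kit counted.

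Observed rate = 40(1 − r)%. Loss = 40r points. Loss as a share of the effect = 40r/31 = 1.29r.

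| r (assumed) | Observed rate | Observed effect (points) | Share of effect lost |
|---|---|---|---|
| 5% | 38% | 29 | 6.5% |
| 10% | 36% | 27 | 12.9% |
| 20% | 32% | 23 | 25.8% |
| 30% | 28% | 19 | 38.7% |

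A tenth of the effect is lost at r = 0.10 × 31/40 = 7.75%. Reading the power section's 0.05 to 0.25 as the two proportions, the corresponding figure is 0.10 × 0.20/0.25 = 8%.

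**6. A force in the other direction.** The article says of the machines: "The vending machines will be available 7 days/week and will be accessible to the public". The power section expects 60% of uptake from community members and 40% from patients. If the 1822 are patients' kits and community kits also enter the numerator, the total is 1822/0.40 = 4555 kits over 4555 encounters, a ratio of 100% instead of 40%. The uncounted share would have to exceed 1 − 40/100 = 60% before undercounting outweighed this.

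**7. Power.** A Hussey–Hughes calculation used four sequences, five periods, ICC 0.02 and 285 per cluster-period, with two-sided alpha 0.05 assumed. Power stays near 1.0 up to r = 50%. If 285 is instead the total over five periods (57 each), power is 0.84 at r = 50%. Power is not the problem.

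**The case against.** The strongest reply is that the power section's proxy has no consent or channel limit, so a kit that clinic staff hand to a decliner is counted under its wording. Table 3 does not label its row as primary. The data analysis section also lists study coordinators and promotores as collectors, which is wider than two channels. This stands as far as it goes: that the kits go uncounted follows from Table 3 and Table 2, not from the power section. But it leaves two stated numerators that disagree, and an analyst could follow either.

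Second, registration is part of the vending strategy as delivered, so a decliner who leaves without a kit is true non-uptake. This stands. Distribution is undercounted only where the decliner then receives a kit that nobody records, and a declined session is not a kit.

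Third, a reader might infer that the primary effect is definitely biased downward. The documents do not support that. They give no refusal rate, do not say where the alternative sources are, and allow public takers to inflate the ratio by up to 2.5 times (step 6). Nor do they describe how baseline kits were issued, beyond their date ruling out consent to this trial.

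Fourth, a journal article may leave tallying details to the full protocol, and Table 3 already plans to report representativeness and reasons for non-participation. Both are fair. Neither reconciles two outcome definitions that the article does state, and neither yields a count of decliners' kits.

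**Conclusion.** The point holds as an inconsistency in how the outcome is counted. The power section and Table 3 define different numerators. Applying Table 3 with the data sources listed would count intervention-period kits more narrowly than the baseline kits they are compared with, so the intervention count can be understated relative to control.

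The size is unknown: 1.29r of the 31-point effect for an uncounted share r, which passes a tenth of the effect at about 8%. This assumes that decliners do obtain kits, that those kits go unrecorded, and that 40% is the rate with all kits counted. The net direction of error in the ratio is not determined. The matter should be settled before data accrue, because kits not tallied when issued may not be recoverable.

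**What to change.** In Table 3 and in the power section, state one numerator for control and intervention periods alike: all RAT kits issued at the clinic or its machine, by any channel, whether or not the taker consents.

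- Keep an anonymous tally by clinic and month of kits given to people who decline registration, with no personal data.
- Restrict consented kits to analyses that need person-level data.
- Tabulate machine sessions that end at the consent step, using the interaction log already planned. Report them descriptively or as a labelled upper bound, never as kits distributed.

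The cost is a few sentences and a tally sheet. The downside is small: decliners' kits carry no covariates and enter only the clinic-month count. The mismatch between community takers and a clinic-visit denominator is a separate matter that this change does not resolve.
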